### Study Objectives

#### Primary Objective

The main aim of this trial is to investigate the impact of adding mobile phone SMS to the usual standard of care versus usual standard of care alone in improving retention in care and promoting adherence to treatment among HIV clients on treatment at 2, 4, and 6 months. Retention in care shall be defined as the proportion of clients who had started on ART, enrolled in the study, and attended clinic visits at the second, fourth, or sixth months. There is no gold standard in the measurement of adherence because the majority of the tools currently used cannot meet all the features of an ideal tool [25]. However, a multi-method tool is recommended and can include self-report and different combinations of other tools including pill count, the pill identification test (PIT) and visual analog scale (VAS), electronic methods, and drug levels. Therefore, a composite adherence measure shall be used in this study to reduce the errors associated with using a single adherence measure [25]. The adherence score shall be built on four adherence measures including a self-report questionnaire with 4 items, supplement of pill pick up from pharmacy refill records, a PIT consisting of 5 items, and a 30-day VAS. Adherence shall first be estimated by each measure and classified into three categories as high, moderate, and low before finally combining the results of the four measures into the composite adherence score.

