### Outcome Measures

#### Primary outcomes

The primary outcomes will be retention in care and adherence to treatments, measured using self-reports (supplemented by PIT, pharmacy refill data, and VAS; Table 1).

**Table 1 table1:** Overview of outcome measures.

Outcome measures			Scale	Type	Measure	Analysis method

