**Primary**						
	Retention at 2, 4, and 6 months		Nominal	Binary	Number retained in care	Risk ratio

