**Overall**						
			Nominal	Binary	Number retained in each group	Risk ratio
			Ordinal	Binary	Change in composite adherence measure	Risk ratio

^a^PRD: pharmacy refill data.

^b^VAS: visual analog scale.

^c^OI: opportunistic infection.

^d^AFB: acid-fast bacilli.

^e^QoL: quality of life.

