### Sample Size Determination

The sample size determination is based on the test of the null hypothesis that the rates of adherence to ART in the intervention and control groups are equal. The primary measure of effect is the rate of adherence to ART as measured by using the VAS over 6 months. Given the information from previous studies [10,11], it is estimated that approximately 60% of participants would maintain adherence ≥95% without intervention and that the interventions would help 82% of the participants maintain ≥95% adherence. A two-sided test is assumed where an effect in either direction will be interpreted at a significance level of 5%. The study will have a power of 80% to yield a statistically significant result using a chi-square test (assuming an intention-to-treat principle for the analysis) of the relative risk at an alpha level of 5% to detect a 25% difference (60% vs 85%).

The formula for calculating the sample size for randomized controlled trials by Chan [26] is used.

where c=7.9 for 80% power and p1 and p2 are the proportion estimates (60% for the control group and 85% for the intervention group).

[figure not shown]

It is assumed that 10% of the participants shall drop out of the study due to loss to follow-up and mortality. A total of 52 participants shall be randomized to each arm to allow for the 10% drop out. Therefore, the required sample size will be 156 (52 x 3 = 156) participants.

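### Retention, a primary outcome, is defined by attendance at month 2, 4 or 6 in one place and at 2, 4 and 6 in others, with no rule for the overall count and no deciding visit

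*Protocol article*

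**What the plan says.** All references are to the Protocol article.

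- **Outcome Measures, Primary outcomes:** "The primary outcomes will be retention in care and adherence to treatments". Retention is therefore a primary outcome in its own right.
- **Study Objectives, Primary Objective, definition:** a single proportion, of clients who had started ART, enrolled and "attended clinic visits at the second, fourth, or sixth months". This is the only definition of retention in the article.
- **Same section, the sentence before:** the aim covers retention and "promoting adherence to treatment among HIV clients on treatment at 2, 4, and 6 months".
- **Table 1, Primary:** "Retention at 2, 4, and 6 months", a binary outcome analysed by risk ratio.
- **Table 1, Overall:** "Number retained in each group", also binary with a risk ratio, without a time point and without saying whether any, all or the last visit counts.
- **Analysis Plan:** tests are two-sided at 5%. The Bonferroni adjustment is stated for secondary outcomes only.

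**The concern.** The definition joins the three visits by *or* within one proportion. Taken at its word, a participant who attends at month 2 and never returns is retained. The intervention runs for 6 months, and its retention messages are timed to each clinic visit, so later loss is a large part of what it is meant to prevent. An outcome that ignores that loss pushes all arms towards 100% and shrinks the difference between them.

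The wording elsewhere points to three separate proportions. That removes the dilution but leaves a different gap: several primary retention results, with nothing to say which one answers the question. Either way, the same data could yield more than one retention result, and the text does not fix the choice.

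**Working it through.** **1. The plan's own figure.** The only sample size in the article rests on adherence, not retention: "The primary measure of effect is the rate of adherence to ART as measured by using the VAS over 6 months". The formula itself is a figure that is not shown. I assume the usual form, with the stated c = 7.9, p1 = 0.60 and p2 = 0.85:

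n = c[p1(1−p1) + p2(1−p2)]/(p1−p2)² = 7.9 × (0.2400 + 0.1275)/0.0625 = 46.45 per arm.

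Allowing for 10% dropout, 46.45/0.9 = 51.6, so 52, which matches the stated 52 per arm and 156 in total. This neither supports nor contradicts anything about retention. It only supplies n = 52 for the illustration.

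**2. One participant under each reading.** Seen at month 2, then lost:

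| Reading | Scored as |
|---|---|
| Any visit (literal *or*) | retained |
| Per visit (*and*, Table 1 Primary row) | retained at month 2; not retained at months 4 and 6 |
| All three visits | not retained |
| Overall row of Table 1 | cannot be scored, as no rule is given |

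The per-visit reading does not produce a single overall number. The only stated retention rule that does is the *or* definition, but the article does not say that the Overall row uses it.

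**3. What the any-visit reading would cost.** The article gives no retention rate by arm or visit, so every rate here is an assumption. With monotone dropout (nobody returns after a missed visit) at a constant rate per two-month interval, r is the proportion kept per interval. Month-6 retention is then r³ and any-visit retention equals month-2 retention, r.

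For month-6 retention of 65% (control) and 85% (SMS): r = 0.65^(1/3) = 0.866 and 0.85^(1/3) = 0.947.

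Power = Φ[(d − 1.96·se0)/se1], with se0 = √(2p̄(1−p̄)/n), se1 = √([p1(1−p1) + p2(1−p2)]/n) and n = 52.

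- Month 6: d = 0.200, se0 = 0.0849, se1 = 0.0826; Φ(0.406) = **66%**.
- Any visit: d = 0.081, se0 = 0.0570, se1 = 0.0565; Φ(−0.544) = **29%**.

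Enumerating all outcomes of the Pearson chi-square test gives 67% and 29%, so the normal approximation is adequate here.

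**4. Range over other assumed rates** (same dropout model, 52 per arm):

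| Month 6, control vs SMS | Power at month 6 | Any visit | Power, any visit |
|---|---|---|---|
| 60% vs 85% | 82% | 84.3% vs 94.7% | 41% |
| 70% vs 90% | 73% | 88.8% vs 96.5% | 33% |
| 80% vs 95% | 64% | 92.8% vs 98.3% | 27% |
| 80% vs 90% | 30% | 92.8% vs 96.5% | 13% |

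In each row, any-visit power is about half of month-6 power or less. In the first row, the number per arm for 80% power rises from 49 to 136.

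**5. What the per-visit reading would cost.** There is no dilution at month 6. There are instead three primary retention results plus the Overall row. None is named as decisive, and the stated multiplicity adjustment does not reach them.

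**The case against.** The strongest reply is that the *or* is distributive: the proportion attending at month 2, at month 4, or at month 6, whichever is being reported. The sentence before it, Table 1 and the Duration section, which schedules an assessment at each of these visits, all fit that reading. Later loss is then visible at months 4 and 6. A condensed article may also leave the derivation of a summary row to a fuller document.

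Much of this stands. A reader might infer that the protocol adopts an any-visit endpoint and that retention therefore cannot show an effect. The documents do not support that. Any-visit is the literal reading of one sentence, not the only reading of the article, and even under it power is reduced, not removed. Nor do they support a starker figure. Scoring the any-visit outcome at 90% vs 95% gives about 16% power, but that pair is freely chosen and does not follow from 65% vs 85% at month 6 under constant monotone dropout, which gives 29%. No stated power for retention is contradicted, because the trial was sized on adherence.

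The reply does not dispose of the point. The article does define this primary outcome, and the definition conflicts with its own statement of the aim and with Table 1. This is a definition fixed badly, not a detail left out. The distributive reading also leaves the Overall row without a rule and the deciding visit unnamed.

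**Conclusion.** The point holds as an inconsistent definition of a primary outcome. What is certain from the text is the *or* against the *and*, an Overall row with no visit rule, no named deciding visit, and a Bonferroni adjustment limited to secondary outcomes.

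The size is conditional. If the literal reading were used, power for retention would fall to about half or less of its month-6 value, for example from about 66% to about 29%. That rests on assumed retention rates, constant monotone dropout and 52 per arm. If the per-visit reading were used, this loss does not arise at month 6, and the problem becomes a choice among several unadjusted primary results.

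**What to change.** Replace the definition in the Primary Objective section with one primary retention rule. One suitable form is attendance at the month-6 clinic visit, out of all randomised, with death and loss to follow-up counted as not retained. This fits the 6-month aim and the intention-to-treat principle in the Analysis Plan. Report months 2 and 4 as supportive, and make the Overall row of Table 1 that same month-6 count. Requiring attendance at all three visits would also resolve the conflict. Deleting the *or* alone would not, because that does not select a visit.

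The Results section reports data collection and analysis as ongoing, so fix the rule before unblinded results are seen, or else date and disclose the choice. The cost is wording only, since the article already schedules assessments at all three months. The reported retention percentage will be lower than under an any-visit count.

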#### Secondary Objectives

The secondary objectives include comparing health outcomes such as weight, BMI, opportunistic infections such as tuberculosis, and quality of life. These comparisons will be performed between the groups at baseline and at 2, 4, and 6 months. In addition, the viral load will be determined for participants who have been receiving ART for at least 6 months to ascertain virologic suppression.

### Outcome Measures

#### Primary outcomes

The primary outcomes will be retention in care and adherence to treatments, measured using self-reports (supplemented by PIT, pharmacy refill data, and VAS; Table 1).

**Table 1 table1:** Overview of outcome measures.

Outcome measures			Scale	Type	Measure	Analysis method
**Primary**						
	Retention at 2, 4, and 6 months		Nominal	Binary	Number retained in care	Risk ratio
	**Adherence at baseline and at 2, 4, and 6 months**					
		Self-report	Ordinal	Binary	% adherence in last month >95%	Risk ratio
		Pill identification test	Ordinal	Binary	% of pills identified >95%	Risk ratio
		PRD^a^	Ordinal	Binary	% of complete refills >95%	Risk ratio
		VAS^b^	Ordinal	Binary	VAS percentage >95%	Risk ratio
**Secondary**						
	Weight		Ratio	Continuous	Change in weight	*t* test
	BMI		Ratio	Continuous	Change in BMI	*t* test
	Viral load		Ratio	Continuous	Change in viral load	*t* test
	OIs^c^ (AFB^d^ diagnosis)		Nominal	Binary	Occurrence of new OI (AFB positive smear)	Chi-square test
	Mortality		Nominal	Binary	All deaths	Chi-square test
	Satisfaction with care		Ordinal	Categorical	Change in satisfaction scores	*t* test
	QoL^e^		Ordinal	Categorical	Change in QoL scores	*t* test

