**Methods:**

This is a multisite randomized controlled single-blinded trial. Computer-generated random block sizes shall be used to produce a randomization list. Participants shall be randomly allocated into the intervention and control groups determined by serially numbered sealed opaque envelopes. The 156 participants will either receive the mobile phone text message or usual standard of care. We hypothesize that sending weekly motivational SMS reminders will produce a change in behavior to enhance retention; treatment adherence; and, hence, health outcomes. Participants shall be evaluated and data collected at baseline and then at 2, 4, and 6 months after the launch of the intervention. Text messages shall be sent out, and the delivery will be recorded. Primary outcome measures are retention in care and adherence to treatment. Secondary outcomes are clinical (weight, body mass index), biological (virologic suppression, tuberculosis coinfection), quality of life, treatment discontinuation, and mortality. The analysis shall be by intention-to-treat. Analysis of covariates shall be performed to determine factors influencing outcomes.

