### Randomization

This is a parallel-group design evaluating the effects of adding once-weekly mobile phone text messages and twice-weekly mobile phone text messages to the usual standard of care (intervention) versus usual standard of care alone (control) among HIV clients receiving ART. Eligible and consenting participants shall be randomized to interventions and control arms using a 1:1:1 allocation ratio by the opaque sealed envelope method. A computer-generated randomization list will be produced using random block sizes of 2, 4, and 6 by the research biostatistician. The allocation codes shall then be put in serially numbered opaque sealed envelopes and administered by the research staff at the various hospitals. Trained interviewers, who shall be blinded to group allocation, will collect data using pretested questionnaires containing sociodemographic data, clinical information, retention, and adherence measures at baseline and at 2, 4, and 6 months. The biostatistician shall also be blinded to group allocation. Blood samples will be collected and analyzed for viral load during the trial once a participant has been on ART for at least 6 months. The time schedule of enrollment, interventions, and assessments are summarized in Figure 1.

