### Participants: Inclusion and Exclusion Criteria

The study population shall include HIV clients either coinfected with or without tuberculosis who come to the hospital for a routine health evaluation. Participants shall be consecutively recruited and randomly allocated to the intervention and control groups.

We shall include clients who are 21 years or older, have access to or own a mobile phone and can read text messages, and who have been on ART for at least a month and planned to live in Cameroon during the period of the study. We shall place more emphasis on clients who have started ART for at least 1 month to measure the differential effects for clients initiating ART versus those who have been under treatment for longer durations. Informed consent is a prerequisite for participating in the study and shall be provided orally and in writing.

We shall exclude clients who have been on ART for less than a month and who are younger than 21 years. Clients who have used ART for at least 1 month are chosen to enable us to be able to calculate a baseline figure for treatment adherence.

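### Table 1 tests change in viral load, but the sampling rule gives recent ART starters no baseline value, and virologic suppression, the endpoint named elsewhere, has no Table 1 row or threshold

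*Protocol article*

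**What the plan says.** The protocol article describes viral load in several places.

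- **Table 1, Secondary:** the measure is "Change in viral load", with ratio scale, continuous type and a t test. There is no row for suppression. The Secondary Outcomes text says that Table 1 summarises the trial endpoints.
- **Randomization:** "Blood samples will be collected and analyzed for viral load during the trial once a participant has been on ART for at least 6 months".
- **Secondary Objectives:** "the viral load will be determined for participants who have been receiving ART for at least 6 months to ascertain virologic suppression".
- **Abstract, Methods:** the secondary outcomes include "biological (virologic suppression, tuberculosis coinfection". The Secondary Outcomes section lists viral load instead and does not mention suppression.
- **Inclusion and Exclusion Criteria:** clients are eligible "who have been on ART for at least a month", and the stated reason for the emphasis on ART duration is "to measure the differential effects for clients initiating ART versus those who have been under treatment for longer durations".
- **Analysis Plan:** binary outcomes in general are reported as a risk ratio with a 95% confidence interval, missing data are handled by multiple imputation, and secondary tests are Bonferroni-adjusted.

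The text gives no suppression threshold and describes no baseline or repeat viral load measurement.

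**The concern.** A change needs two values per person, and a change from baseline needs one of them at entry. The sampling rule withholds the entry value from everyone who has not yet reached 6 months of ART. The one analysis that the table specifies for viral load therefore cannot be computed from observed data in those participants.

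Two things are at stake. First, recent starters are one side of a comparison that the plan says it wants to make, and they are the people who would contribute nothing to this analysis. Second, the endpoint is named in two ways. The abstract and the Secondary Objectives point to a yes/no outcome, while Table 1 points to a continuous change. An analyst would have to choose between them, and would have to choose a cut-off for suppression, with the data in hand.

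**Working it through.** **The plan's own figures.** No number is stated for viral load. The only sample-size calculation concerns adherence on the visual analog scale, with c = 7.9, 60% and 85%: 7.9 × (0.60 × 0.40 + 0.85 × 0.15) / 0.25² = 7.9 × 0.3675 / 0.0625 = 46.45 per arm. Allowing for 10% dropout, 46.45 / 0.9 = 51.6, which rounds up to the stated 52. That figure reproduces and does not bear on this point.

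**Inputs.**
- Minimum ART at entry: 1 month (Inclusion and Exclusion Criteria).
- Sampling rule: at least 6 months of ART (Randomization; Secondary Objectives).
- Visits: baseline and months 2, 4 and 6 (Duration).

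**Check.** With m months of ART at entry, viral load can be taken at visit t only if m + t ≥ 6.

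| ART at entry (months) | Visits that qualify | Baseline value possible? |
|---|---|---|
| 1 | 6 | No |
| 2 or 3 | 4, 6 | No |
| 4 or 5 | 2, 4, 6 | No |
| 6 or more | 0, 2, 4, 6 | Yes |

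At 1 month of ART only one visit qualifies, so no change of any kind can be formed. At 2 to 5 months two or more visits qualify, but all fall after the intervention has begun, so any difference between them is not a change from baseline. At 6 months or more a change from baseline is possible, though the text does not schedule it.

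**How many are affected.** The share entering with at least 6 months of ART is not given. As an assumption, take 50%, 70% or 90% of the planned 52 per arm:

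| Assumed share | Per arm with a possible baseline value | Without one, of 156 |
|---|---|---|
| 50% | 26 | 156 − 3 × 26 = 78 |
| 70% | 36 | 156 − 3 × 36 = 48 |
| 90% | 47 | 156 − 3 × 47 = 15 |

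**Month 6.** The shortest ART duration of anyone still on treatment at the last visit is 1 + 6 = 7 months. This exceeds 6, so the sampling rule excludes none of them at that visit.

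**The case against.** The strongest reply is that suppression does have an analysis, because the Analysis Plan assigns a risk ratio, a confidence interval and intention-to-treat handling to every binary outcome. This stands in part. It would be wrong to say that suppression has no analysis at all; what it lacks is a Table 1 row and a threshold. The general rule does not settle the matter, since Table 1 classes viral load as continuous and assigns it a different test. A threshold might sit in a fuller document, but the mismatch between the stated endpoint and the stated analysis is in this one.

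Figure 1, which carries the schedule, is not shown, and the text speaks of blood samples without a number per person. More than one sample may therefore be planned. That would supply an entry value for recent starters only if the figure departed from the 6-month rule in the text.

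Multiple imputation does not rescue the change analysis. Under the rule, no participant with under 6 months of ART has an observed baseline value, so the imputation would rest entirely on extrapolation from longer-treated clients.

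Three stronger readings are tempting and are not supported.

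- **That the t test itself has little power.** A simulation with assumed inputs (50 per arm, 40 copies/mL if suppressed, unsuppressed log10 mean 4.5 and SD 0.8, suppression 75% vs 90%) gives power of about 10% for a t test on raw values, 49% on log10 values and 54% for a chi-square test on suppression. The gap comes mainly from the raw scale, which Table 1 does not specify, and the simulation compares single values rather than change.
- **That viral load is the trial's only objective check on adherence.** Pharmacy refill records and the pill identification test are not self-report either.
- **That recent starters go unmeasured.** They lose a baseline value, not a measurement; those still on ART at month 6 qualify for a sample.

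**Conclusion.** The point holds as an inconsistency in a stated secondary analysis. Under the sampling rule as written, every participant entering with 1 to under 6 months of ART lacks a baseline viral load and cannot contribute an observed change from baseline. The outcome named in the abstract and the Secondary Objectives is missing from the table said to summarise the endpoints, and has no cut-off.

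The logical part rests only on the document's own entry rule, sampling rule and visit times. The count (15 to 78 of 156) rests on an assumed share of longer-treated clients from 90% down to 50%. The primary outcomes and the sample size are unaffected. The row should be corrected before the viral load data are analysed.

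**What to change.** Replace the Table 1 viral load row with virologic suppression (yes/no, at a stated copies/mL threshold) at month 6, or at the available sample nearest month 6 where sampling is already done. Analyse all randomised participants and report a risk ratio with 95% CI by arm, adjusted for ART duration at entry (under 6 months vs 6 months or more). Name the endpoint identically in the abstract, Secondary Objectives, Secondary Outcomes and Table 1.

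Keep the plan's multiple imputation as the main handling of missing values, and add a sensitivity analysis that counts a missing value as not suppressed. If a continuous analysis is retained, use log10 values and limit change to participants with a baseline value. Retaining it as well as suppression would add one test to those covered by the Bonferroni adjustment.

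The cost is one table row, a threshold and consistent wording. The downside is timing. Allocation was in July 2018 with 6 months of follow-up, so visits would nominally have ended about January 2019 and samples probably cannot be re-timed. Where blood was drawn early, the nearest-sample rule leaves unequal sampling times, which should be reported by arm.
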